### Randomization

All enrolled patients will be randomly assigned to either the intervention or control groups in a 1:1 ratio. The random number sequence will be generated using the Statistical Product and Service Solutions (IBM SPSS, V.20.0) statistical software. Grouping information will be securely stored in opaque envelopes.

### Blinding

The independent research assistant will have the responsibility of explaining the procedure and details of IMT and measuring the Pi(max) for all participants. The research assistant will conduct remote instruction and real-time monitoring of the participants through video software, making them unblinded to the process. However, both the participants and the research assistant will be explicitly instructed not to disclose any details to other researchers involved in the study.

On the other hand, the anesthesiologist, the endoscopist, data collectors, laboratory technicians, and biostatistician will be blinded to the intervention protocols and group allocation to ensure unbiased evaluation.

### Sample size

We based our calculations on an incidence of the primary endpoint at 40% in the control group and 20% in the intervention group. As a result, we arrived at a revised sample size of 105 participants for each group to yield 90% power with a type I error of 0.05. Anticipating a potential dropout rate of 10%, our target enrollment is set at 232 participants in total, evenly distributed with 116 participants per group for the study.

### Statistical analysis

An independent biostatistician, not involved in our trial, will analyze all the data using optimal software. We will use the Last Observation Carried Forward (LOCF) imputation method to handle missing data. However, this study will not include interim analyses.

Continuous variables will be assessed using either the *t*-test or Wilcoxon rank test, depending on the nature of the data. For the analysis of counting data, the chi-square test or Fisher’s exact test will be employed for comparison. Statistical significance will be defined as *p*<0.05.

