**Outcome assessment**										
(1) The incidence of hypoxemia					X					
(2) The need for airway maneuvers					X					
(3) Blood pressure		X		X	X		X			
(4) Sleep quality		X		X				X	X	X
(5) Pro-inflammatory cytokines levels		X		X		X				
(6) Adverse events					X		X			
**Requirement for vasoactive agents**					X		X			
**Need for rescue sedatives**					X		X			

IMT, inspiratory muscle training; PACU, post-anesthesia care unit; Pi(max), maximum inspiratory pressure; MOAA/S, Modified Observer’s Assessment of Alertness and Sedation; BIS, bispectral index; T1, 1 day before IMT; T2, immediately prior to anesthesia; T3, at the conclusion of the gastroscopy; T4, on the night of the gastroscopy; T5, 1 week after the gastroscopy; T6, 4 weeks after the gastroscopy.

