### Participant enrollment

Between September 2023 and August 2024, potential subjects for this study will be recruited from the outpatient clinic of the Department of Anesthesiology. This clinic handles a monthly volume of over 2000 patients undergoing painless gastroscopy, and the prevalence of obesity in this population exceeds 1 percent. Out of the eligible candidates, a total of 232 patients will be enrolled. Before enrollment, these individuals will receive comprehensive information regarding the study’s purpose, procedures, considerations, potential benefits and risks, as well as any associated costs. They will be fully informed and have the opportunity to provide voluntary consent to participate. Both the subjects and their authorized representatives will be responsible for maintaining the confidentiality of the received protocol. Written informed consent will be obtained from all subjects prior to their enrollment. Participants will have the freedom to withdraw from the study at any point without incurring any liability, and such withdrawal will not impact their subsequent gastroscopy procedures.

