### Primary outcomes

The primary outcome of this study is the incidence of hypoxemia during painless gastroscopy. Hypoxemia will be defined as a SpO_2_ level below 90%.

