### Secondary outcomes

The secondary outcomes encompass several measures, including the need for airway maneuvers, blood pressure changes, sleep quality assessment, pro-inflammatory cytokine levels, and monitoring of adverse events such as bradycardia, tachycardia, nausea, and vomiting.

For this study, airway maneuvers will be defined as jaw-lift, positive-pressure ventilation with a bag-mask, insertion of a laryngeal mask, or endotracheal intubation.

Blood pressure will be measured at different time points: before IMT, prior to anesthesia, during the examination, and in the PACU.

Sleep quality and duration will be assessed using the Pittsburgh Sleep Quality Index (PSQI), a 19-item questionnaire (Table 3), at T1, T2, T4, T5, and T6. A patient scoring greater than 5 on the PSQI will be classified as a poor sleeper (35).

**Table 3 tab3:** The questionnaire of Pittsburgh Sleep Quality Index.

1. During the past month, when have you usually gone to bed?				
2. During the past month, how long (in minutes) has it taken you to fall asleep each night?	≤15 min (0)	16 ~ 30 min (1)	31 ~ 60 min (2)	>60 min (3)
3. During the past month, when have you usually gotten up in the morning?				
4. During the past month, how many hours of actual sleep did you get that night? (This may be different than the number of hours you spend in bed)	>7 h (0)	6 ~ 7 h (1)	5 ~ 6 h (2)	<5 h (3)
5. During the past month, how often have you had trouble sleeping because you…	Not during the past month (0)	Less than once a week (1)	Once or twice a week (2)	Three or more times a week (3)
a. Cannot get to sleep within 30 min	(0)	(1)	(2)	(3)
b. Wake up in the middle of the night or early morning	(0)	(1)	(2)	(3)
c. Have to get up to use the bathroom	(0)	(1)	(2)	(3)
d. Cannot breathe comfortably	(0)	(1)	(2)	(3)
e. Cough or snore loudly	(0)	(1)	(2)	(3)
f. Feel too cold	(0)	(1)	(2)	(3)
g. Feel too hot	(0)	(1)	(2)	(3)
h. Have bad dreams	(0)	(1)	(2)	(3)
i. Have pain	(0)	(1)	(2)	(3)
j. Other reason(s), please describe, including how often you have had trouble sleeping because of this reason(s)	(0)	(1)	(2)	(3)
6. During the past month, how often have you taken medicine (prescribed or “over the counter”) to help you sleep?	Not during the past month (0)	Less than once a week (1)	Once or twice a week (2)	Three or more times a week (3)

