### Data collection, handling, and monitoring

We will gather the following data for this study:

Demographic data, including age, gender, and ASA physical status classifications.Physical examination data, including HR, mean arterial pressure (MAP), SpO_2_, respiratory rate, end-tidal carbon dioxide levels, Pi(max), BMI, neck circumference, and waist-hip ratio.Data related to the primary and secondary outcomes as mentioned earlier.Requirement for vasoactive agents, such as atropine, esmolol, phenylephrine, and urapidil hydrochloride.Need for rescue sedatives.

In order to prevent any loss of follow-up, a research assistant who knows the group assignment will reach out to patients from time to time. Their purpose is to remind patients to fill out the PSQI sheets.

To ensure data integrity and security, an independent monitor will oversee the data collection process. Data collectors will enter all raw data into Excel spreadsheets, which will then be stored in a separate database with restricted access using passwords. Additionally, original data and images will be securely stored on the research center’s computer, accessible only with login passwords. Unauthorized access to the database or computer will be strictly prohibited without the monitor’s permission.

In case of any adverse events, immediate attention will be given, followed by detailed recording and continuous follow-up. The Ethics Committee will periodically review the project’s progress and decide whether it should be continued.

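### LOCF is the only missing-data method named, but hypoxemia is assessed once, so LOCF cannot validly supply a missing primary outcome

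*Protocol article*

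**What the plan says.** The Statistical analysis section gives one rule: "We will use the Last Observation Carried Forward (LOCF) imputation method to handle missing data". It does not limit the rule to repeated measures, and the article states no other.

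Under Primary outcomes, "The primary outcome of this study is the incidence of hypoxemia during painless gastroscopy", and "Hypoxemia will be defined as a SpO_2_ level below 90"%. In Table 1 the row "1) The incidence of hypoxemia" has a single mark, in the anesthesia and examination period. SpO2 itself is recorded earlier. Data collection lists "Physical examination data, including HR, mean arterial pressure (MAP), SpO_2_, respiratory rate", and Table 1 schedules vital signs at screening, at T1 (the day before training) and at T2 (just before anesthesia).

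Several sections bear on patients who leave:
- Sample size: "Anticipating a potential dropout rate of 10%, our target enrollment is set at 232 participants in total".
- Participant enrollment: a patient may withdraw at any time, and "such withdrawal will not impact their subsequent gastroscopy procedures".
- Participants' inclusion and exclusion criteria: subjects who meet a shedding criterion are excluded from the study.
- Shedding criteria: these cover withdrawal at any stage and also severe hypoxemia that leads to intubation.

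Some secondary outcomes are repeated: PSQI "at T1, T2, T4, T5, and T6", cytokines at T1, T2 and T3, and blood pressure from before training to the PACU.

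**The concern.** LOCF needs an earlier measurement of the same variable. Hypoxemia under sedation has none, because the event can only occur during the one procedure. The four-week training period comes before that procedure, so a patient who leaves during training has no primary outcome and the stated rule does not say what to do.

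The risk is that an analyst applies the rule literally, takes the last recorded SpO2 (awake, before sedation), finds it at or above 90% and enters no event. Each dropout then counts as a success. One arm trains against a load that rises weekly and the other trains without load, so dropout could differ between arms. In that case the scoring favours the arm that loses more patients. For repeated secondary outcomes LOCF can be applied, but it fixes the patient at the last value and understates uncertainty.

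**Working it through.** **Inputs.** From Sample size: 40% control, 20% intervention, 90% power, type I error 0.05, 105 per group, 10% dropout, 116 per group. From Statistical analysis: chi-square or Fisher's exact test. Assumed: a two-sided test. The document gives no dropout by arm, so all unequal splits below are assumptions that average its 10%.

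**The plan's own figure.** Unpooled two-proportion formula: n = (1.960 + 1.282)² × (0.4×0.6 + 0.2×0.8) / 0.20² = 10.507 × 0.40 / 0.04 = 105.07, which matches 105. Dropout: 105 × 1.10 = 115.5, rounded up to 116. The sample size is not in question here.

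**How many patients.** 10% of 232 is about 23 patients who could lack the primary outcome.

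**Reading A: nothing is carried.** There is no earlier hypoxemia assessment, so dropouts stay missing and the analysis is on complete cases. About 104 per arm remain (116 × 0.90 = 104.4). Exact power of the chi-square test at 40% vs 20% is 89.2%, against 92.0% at 116 per arm with nobody missing.

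**Reading B: an awake SpO2 is carried.** This requires the carried value to be 90% or above. The document does not say so, but it is likely in ASA I–II patients before sedation. The expected rate in each arm becomes p × (1 − dropout), with 116 retained. Rejection probabilities are exact for the two-sided chi-square test.

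| True rates | Dropout, control / training | Rates after scoring | Rejection probability |
|---|---|---|---|
| 40% vs 20% | 10% / 10% | 36% vs 18% | 87.7% (power) |
| 40% vs 20% | 15% / 5% | 34% vs 19% | 73.9% (power) |
| 40% vs 40% | 10% / 10% | 36% vs 36% | 4.9% (type I error) |
| 40% vs 40% | 8% / 12% | 36.8% vs 35.2% | 5.6% (type I error) |
| 40% vs 40% | 5% / 15% | 38% vs 34% | 9.6% (type I error) |

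With equal dropout the risk difference shrinks from 20 to 18 points. Power is 89.2 − 87.7 = 1.5 points below the complete-case analysis, and type I error is unharmed. Only unequal dropout inflates type I error, and the amount depends strongly on the split.

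**Secondary outcomes.** A missing T3 cytokine value would be filled from T2 or T1, and a missing T4 PSQI from T2 or T1, all before the procedure. A missing T5 or T6 PSQI would normally be filled from T4 or T5, which are after it. In every case the filled value assumes no change and enters the test as if observed, so standard errors are too small.

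**The case against.** The strongest reply is that Reading B is not what the trial intends. Withdrawn subjects are to be excluded under the shedding criteria, and inflating 105 to 116 per group makes sense only if dropouts leave the primary analysis. An awake SpO2 is not an earlier observation of hypoxemia during gastroscopy, and nothing in the document says it will be carried into the endpoint. The 9.6% also depends on a 5%/15% split, while the document gives only an overall 10% and describes the training as well tolerated.

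Most of this stands. A reader might infer that the plan will score dropouts as free of hypoxemia and so nearly double the false-positive rate. The document does not support that as a prediction: Reading A fits its other sections better, and the inflation needs an assumed imbalance. Nor does it support two further inferences. LOCF does not always carry a pre-procedure value over a post-procedure one, as the T5 and T6 PSQI show. And it is not established that most of the missingness is avoidable: withdrawal leaves the patient's gastroscopy unaffected, but nothing says that it will be at this center or that data may be used after consent is withdrawn.

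The reply does not rescue the rule. On Reading A the only stated method does nothing for the primary outcome, and the default is to drop randomised patients. Detail left to a statistical analysis plan would not cure this, because the article already fixes a method, and it is the wrong kind for this endpoint.

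**Conclusion.** The concern holds in this form: LOCF, named without restriction as the sole missing-data method, cannot validly supply a missing primary outcome that is assessed once. The document leaves two readings open and favours the complete-case one.

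The size depends on the reading. If dropouts are scored as event-free, equal dropout costs a little power and no type I error. Harm to type I error ranges from slight to nearly double the nominal level over the assumed splits, and the direction of bias depends on which arm loses more patients. These figures rest on a two-sided chi-square test, 116 per arm and carried SpO2 values of at least 90%. For repeated secondary outcomes LOCF can be applied but is a poor choice, most clearly for T3 cytokines and T4 PSQI.

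A related risk needs no assumption about dropout. Patients shed after intubation for severe hypoxemia have already had the primary event, and either excluding them or carrying a pre-sedation value would erase it.

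**What to change.** Delete LOCF.

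For the primary outcome:
- Analyse all randomised patients as allocated.
- Keep every observed hypoxemia event, including those of patients shed after intubation for severe hypoxemia.
- Record the gastroscopy SpO2 of patients who stop training, where they consent and the procedure is done at the center.
- Handle outcomes still missing by multiple imputation from baseline variables already collected (age, sex, BMI, neck circumference, waist-hip ratio), with a best/worst-case or tipping-point sensitivity analysis.

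For PSQI, cytokines and blood pressure, fit a likelihood-based mixed model to the observed data, with no single imputation.

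The cost is revised analysis wording and a little more programming. SpO2 is already monitored at the study gastroscopy, and neither the sample size nor the treatment changes.

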**Score of Pittsburgh Sleep Quality Index**		

This scale is designed to record your own assessment of any sleep difficulty you might have experienced. Please complete this scale at T1, T2, T4, T5, and T6. All scales will be finally e-mailed to designated anesthesiologist. (T1: one day before inspiratory muscle training, T2: the moment before anesthesia, T4: the night of gastroscopy, T5: 1 week after gastroscopy, T6: 4 weeks after gastroscopy).

At three different time points, namely T1, T2, and T3, 5 mL of venous blood will be collected from the patient’s elbow. The collected blood samples will be processed through conventional centrifugation to separate the plasma. Subsequently, radioimmunoassay will be employed to measure the plasma levels of pro-inflammatory cytokines, including tumor necrosis factor-alpha (TNF-α) and interleukin-6 (IL-6).

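### Blood pressure, PSQI and cytokines each have a pre-training value and two to four later values, but the stated two-sample test makes no stated use of that baseline and singles out no visit

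*Protocol article*

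**What the plan says.** The Statistical analysis section of the protocol article has one rule for all continuous variables: a t-test or "Wilcoxon rank test, depending on the nature of the data". It then fixes one threshold for everything ("Statistical significance will be defined as" p<0.05) and handles missing data by LOCF. It names no baseline covariate, no model for repeated measurements and no key time point.

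The schedule of measurements is richer than that rule. The footnote to Table 1 defines the first time point as "T1, 1 day before IMT", so T1 is a true pre-intervention baseline. The Secondary outcomes section then gives:

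- Blood pressure: "Blood pressure will be measured at different time points: before IMT, prior to anesthesia, during the examination, and in the PACU". That is one baseline and three later values.
- PSQI: "at T1, T2, T4, T5, and T6. A patient scoring greater than 5 on the PSQI will be classified as a poor sleeper". That is one baseline and four later values.
- Cytokines (TNF-alpha and IL-6): "At three different time points, namely T1, T2, and T3, 5 mL of venous blood will be collected". That is one baseline and two later values for each.

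The Abstract and the Secondary outcomes section describe the blood pressure outcome as changes in blood pressure. No change score is defined, and the term is not used for PSQI or the cytokines.

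**The concern.** A two-sample t-test or Wilcoxon test takes one number per patient and has no place for a covariate. Applied to a later value, it leaves between-patient variation in the error term that the T1 value could have removed. Applied to several visits, it gives a separate p-value for each, with no rule on which one carries the conclusion.

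Two things are at stake. The first is precision: five questionnaires and three blood samples per patient are already planned, and part of their information would go unused. The second is interpretation: with several visits per outcome and none named, a reader of the results cannot tell a planned comparison from the most favourable one.

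**Working it through.** **The plan's own figure.** The only sizing in the article is for the binary primary outcome, based on "an incidence of the primary endpoint at 40% in the control group and 20% in the intervention group", with 90% power and type I error 0.05 (taken as two-sided). With unpooled variance, n = (0.4×0.6 + 0.2×0.8) × (1.960 + 1.282)² / 0.20² = 105.07 per group. The stated 105 is reproduced. The continuous outcomes have no sizing of their own, so 105 per group is used below as the number analysed.

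**Step 1: variance with and without T1.** Let r be the correlation between the T1 value and the later value. The documents do not give it, so a range is assumed, with equal variance at both times. Relative to comparing later values alone (factor 1):

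- adjusting for T1 (ANCOVA): 1 − r²
- change from T1: 2(1 − r)

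| r | ANCOVA | Change score | Per-group n at which the unadjusted test matches ANCOVA, 105/(1 − r²) |
|---|---|---|---|
| 0.3 | 0.91 | 1.40 | 115 |
| 0.5 | 0.75 | 1.00 | 140 |
| 0.7 | 0.51 | 0.60 | 206 |
| 0.8 | 0.36 | 0.40 | 292 |

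Since 2(1 − r) − (1 − r²) = (1 − r)², which is never negative, ANCOVA is never less efficient than the change score. Below r = 0.5 the change score is worse than ignoring T1.

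**Step 2: the same in power.** With 105 per group, the unadjusted test has 80% power for a difference of (1.960 + 0.842) × √(2/105) = 0.387 SD. For that difference ANCOVA would have about 84%, 90%, 97.5% and 99.7% power at r = 0.3, 0.5, 0.7 and 0.8.

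**Step 3: number of tests.** Suppose each later visit is tested, with one blood pressure parameter and PSQI as a score. The count is 3 + 4 + 2×2 = 11.

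- All tests independent: 1 − 0.95¹¹ = 43.1%.
- Test statistics correlated within an outcome and independent between outcomes (simulation, 400,000 replicates): 41.5% at correlation 0.3, 38.8% at 0.5, 34.9% at 0.7 and 32.1% at 0.8.
- One contrast for each of the four outcomes: 1 − 0.95⁴ = 18.5% if independent.

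High correlation is plausible for PSQI. The items in Table 3 ask about the past month, while T2 and T4 fall on the same day and T5 a week later, so the recall windows largely overlap.

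**The case against.** The strongest reply is that little harm follows. Only secondary outcomes are involved; the Discussion speaks of exploring them and calls the trial essentially a pilot. The primary outcome is binary with no baseline, and its sample size is untouched. This stands, and it limits the weight of the point.

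A reader might infer that the stated test is biased or invalid. The documents do not support that. Under randomisation the unadjusted comparison keeps its type I error, and chance imbalance at T1 is already reflected in its standard error. The cost is precision.

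A reader might also infer that T1 is ignored throughout and that 11 tests are planned. Neither is stated. The article names a family of tests, not the variable entered. For blood pressure, changes may well mean change from T1; if so, the advantage of ANCOVA at r = 0.7 is a factor of 0.60/0.51 = 1.18, not 1/0.51 = 1.96. Testing at every visit is the natural reading when several visits are scheduled and none is singled out, but it remains an inference. PSQI may also be analysed through its poor-sleeper cut-off.

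The size of the gain is uncertain too. Blood pressure during the examination is taken under sedation, with vasoactive drugs allowed, so a strong correlation with a value from about four weeks earlier cannot be presumed. At r = 0.3 only 9% of the variance is removed.

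Finally, visit structure and contrasts are commonly left to a statistical analysis plan, which is not shown. That answers a complaint of missing detail. It does not answer the point that the rule the article does state, for all continuous variables, is a weaker choice than the design allows.

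**Conclusion.** The point holds as one of efficiency and clarity for four secondary outcomes, not as an error that threatens the trial's main conclusion. The stated rule gives a valid test, but a better one is available from data already scheduled.

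The gain depends on a correlation that the documents do not give: modest at 0.3 and substantial from 0.5 upwards. The multiplicity figure of about 32% to 43% is conditional on testing every later visit with one blood pressure parameter, and the upper end requires independence, which repeated values on the same patient will not have. Naming one contrast per outcome reduces the problem without removing it: up to about 18.5% remains across the four outcomes.

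**What to change.** In the Statistical analysis section, replace the t-test/Wilcoxon rule for blood pressure, PSQI, TNF-alpha and IL-6 with ANCOVA, or a mixed model for repeated measures (arm, visit, arm-by-visit), with the T1 value as covariate.

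State which blood pressure parameter is analysed. Name one contrast per outcome before unblinding. T2 is a reasonable example for the effect of training, since it follows the four weeks of training and precedes sedation. Report the other visits as estimates with 95% confidence intervals, without significance claims. Whether to log-transform the cytokines is a matter of preference, to be settled in advance.

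No change to the primary analysis is needed on this account. The cost is analysis wording and programming, with no new data, visits or patients.

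### The only test named for the primary outcome is unadjusted: valid, but it leaves unused baseline data that could add a modest, unquantified amount of power at no extra data cost

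*Protocol article*

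**What the plan says.** The Primary outcomes section defines a binary endpoint, SpO2 below 90%: "The primary outcome of this study is the incidence of hypoxemia during painless gastroscopy". For such data the Statistical analysis section names one family of methods: "For the analysis of counting data, the chi-square test or Fisher’s exact test will be employed for comparison". It mentions no covariate-adjusted analysis.

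The Sample size section compares two proportions, assuming "an incidence of the primary endpoint at 40% in the control group and 20% in the intervention group", and arrives at "105 participants for each group to yield 90% power with a type I error of 0.05". Enrollment is then raised for dropout: "Anticipating a potential dropout rate of 10%, our target enrollment is set at 232 participants in total".

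The Randomization section gives the allocation ratio and names no stratification factor: "All enrolled patients will be randomly assigned to either the intervention or control groups in a 1:1 ratio".

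The Data collection section lists "Demographic data, including age, gender, and ASA physical status classifications". Among the physical examination data it lists SpO2 and "end-tidal carbon dioxide levels, Pi(max), BMI, neck circumference, and waist-hip ratio". Table 1 places demographic data, physical examination data and vital signs at screening.

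**The concern.** In a randomised trial with a binary outcome, adjusting for baseline variables that predict the outcome narrows the interval for the treatment effect and raises power at the same sample size. The Introduction attributes hypoxemia in obesity to chest-wall compression, poor lung function, limited oxygen reserve and upper airway obstruction. Neck circumference, waist-hip ratio and baseline SpO2 are plausible markers of those mechanisms, and no entry criterion restricts them directly.

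What is at stake is some precision, plus a settled answer if the arms differ by chance on an airway-risk marker. An adjusted model added only after such an imbalance is seen would be open to criticism as post hoc.

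**Working it through.** **Inputs from the article.** Control 40%, intervention 20%; 105 per arm; 90% power; type I error 0.05 (two-sided assumed, since the side is not stated); 10% dropout; 232 enrolled.

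**Input assumed.** The prognostic strength of the covariates, which the article does not give. A range is shown.

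**Step 1: reproduce the sample size.** The unpooled two-proportion formula gives n = (1.960 + 1.282)² × (0.4×0.6 + 0.2×0.8) / 0.2² = 10.507 × 0.40 / 0.04 = 105.07 per arm, which matches 105. For dropout, 105 × 1.1 = 115.5, so 116 per arm and 232 in total. The sizing therefore has the same unadjusted basis as the named test.

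**Step 2: power of the named tests at 105 per arm.**
- Chi-square, pooled formula: Φ[(0.2 − 1.960 × √(2×0.3×0.7/105)) / √(0.40/105)] = Φ[(0.2 − 0.1240) / 0.0617] = Φ(1.232) = 89.1%.
- Chi-square, exact enumeration: 89.2%.
- Fisher's exact test, exact enumeration: 86.3%.

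**Step 3: adjust for one covariate.** Simulation at 105 per arm, 6,000 trials per row, with marginal risks held at 40% and 20% and one standard-normal baseline covariate. The variance ratio is that of the risk difference, adjusted over unadjusted.

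| Covariate AUC (assumed) | Chi-square | Adjusted logistic, Wald | Standardised risk difference | Variance ratio |
|---|---|---|---|---|
| 0.50 (none) | 89.0% | 88.8% | 89.4% | 1.00 |
| 0.58 | 89.0% | 89.3% | 90.0% | 0.98 |
| 0.63 | 88.3% | 90.0% | 90.6% | 0.95 |
| 0.70 | 88.6% | 91.7% | 92.4% | 0.90 |
| 0.74 | 89.2% | 93.4% | 93.9% | 0.85 |
| 0.81 | 88.9% | 95.9% | 96.3% | 0.73 |

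The Monte Carlo standard error of each power is √(0.89×0.11/6000) = 0.4 points, so the drift in the chi-square column is noise. The gain is about 0 to 1 point for a weak covariate (0.58), 2 to 4 for a moderate one (0.63 to 0.70) and 4 to 7 for a strong one (0.74 to 0.81). For the moderate range the interval narrows by 1 − √0.95 = 2.5% to 1 − √0.90 = 5%.

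**Step 4: does a five-covariate model cost anything?** Expected events are 105×0.4 + 105×0.2 = 63, or about 10 per coefficient for treatment plus five covariates. The model was simulated at 105 per arm with one prognostic covariate and four of pure noise. Power stayed at about 89% with no prognostic value and rose to about 90 to 94% at log-odds of 0.3 to 1.0 per SD, with type I error about 5%. A repeat with 5,000 trials per setting gave, over the same log-odds range, 89.4 to 92.5% for the Wald test of the treatment term and 90.4 to 93.3% for the standardised risk difference. Under no effect (30% in both arms), type I error was 4.8 to 5.3% for the Wald test and 5.4 to 5.9% for the standardised difference with an uncorrected standard error. Part of the latter's apparent advantage is therefore a slightly small standard error.

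**Step 5: chance imbalance.** Assuming simple randomisation, a standardised baseline difference has standard error √(2/105) = 0.138. A difference above 0.2 SD has probability 2 × [1 − Φ(0.2/0.138)] = 2 × [1 − Φ(1.449)] = 14.7%. For at least one of five independent markers it is 1 − (1 − 0.147)⁵ = 55%.

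**The case against.** The strongest reply is that nothing here is wrong. Allocation is 1:1 with no stratification factor named, so no covariate has to enter the analysis. The chi-square test matches the sample-size basis and delivers about 89%. The distance from 90% is about one point and comes from using the unpooled rather than the pooled variance. Chance imbalance is already allowed for in the test's type I error. A journal article may also leave adjusted models, effect estimates and intervals to an analysis plan that is not shown. All of this stands, and it limits the point to an improvement.

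A reader might go further and infer that strong risk markers are being ignored and power thrown away. The article does not support that. It reports no association between any of the listed variables and hypoxemia in this population; the Introduction speaks of obesity in general. BMI is held to 35 to 39.9, age to 18 to 50 and ASA class to I or II, and known difficult airways are excluded. All of this weakens those markers within the trial. The 4 to 7 point gains in the table should not be expected on this evidence.

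The worry that five covariates would overload the model with about 63 events is fair to raise, but Step 4 shows essentially no loss. A further caution stands: not every recorded value is a proper baseline. SpO2 at T2 follows four weeks of training. For Pi(max), the Intervention section describes measurement in the intervention group, whereas the Blinding section has it measured in all participants.

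**Conclusion.** The point holds as a free improvement. The one family of methods named for the primary outcome is valid but makes no use of plausibly prognostic data already scheduled at screening. The likely gain over chi-square is 0 to 1 point of power for weak covariates and 2 to 4 points for moderate ones, from about 89%. A moderate covariate would be enough to reach the stated 90%. Against Fisher's exact test, which the text also permits, the starting point is about 86%.

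These figures rest on an assumed prognostic strength, 40% against 20%, 105 evaluable per arm and a two-sided 0.05 level. If the covariates carry no information, the result is essentially unchanged. If the unseen analysis plan already has an adjusted primary analysis, what remains is to bring the published method into line with it.

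**What to change.** Before unblinding, prespecify the primary analysis as a logistic regression of hypoxemia on treatment and a short fixed list of pre-randomisation covariates, for example neck circumference, screening SpO2, BMI, age and sex.

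- Report the standardised (marginal) risk difference and risk ratio with 95% confidence intervals. Use a small-sample correction to the standard error, or take the p-value from the treatment term, given the type I error in Step 4.
- Keep the chi-square test as the supporting unadjusted analysis.
- State that the SpO2 covariate is the screening reading and not the T2 reading.
- Leave Pi(max) out of the model until the Intervention and Blinding sections are reconciled on who is measured.

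The cost is one paragraph of analysis text and slightly more analysis work. No extra patients, visits or measurements are needed.
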